## Sample size

In this prospective observational study, we aim to recruit all patients with available data who fulfil the inclusion criteria and are admitted to Children’s Hospital 1 in Ho Chi Minh City in Vietnam from 2017 to 2019. Based on retrospective surveillance data, we estimate recruitment of 800 participants during the study period. Blood cultures will be performed in all cases, we expect to yield ~400 bacterial isolates.

### Participant selection and recruitment

#### Inclusion criteria

Neonates (≤1 month of age) with a diagnosis of ‘probable’ or ‘confirmed’ sepsis who have had a blood culture taken and who are an inpatient at Children’s Hospital 1 will be recruited into the study after written informed consent has been given by a parent or guardian.

### Exclusion criteria

Patients will be excluded when informed consent is not provided, the length of hospital stay less than 24 hours, imminent and inevitable death or the patient has been previously recruited in the study. Investigators will review all of the mortality records during the time period of the study to try and identify how many of these cases may have been missed and whether there were any common characteristics in these participants.

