### Sepsis and AMR in Vietnam

Bacterial sepsis is classified into two major groups according to place of acquisition. Hospital-acquired sepsis is defined in patients with clinical manifestations of sepsis and a confirmatory blood culture collected >48 hours following hospital admission.^12^ Hospital-acquired sepsis is a major threat to patient safety, and in locations with poor surveillance and infection control programme such infections are associated with high mortality rates. The incidence of AMR bloodstream infections in Vietnam has increased over recent years and is predicted to increase further.^13^ This trend has comprised an increase in both Gram-negative and Gram-positive pathogens, chiefly *Escherichia coli, Klebsiella pneumoniae, Acinetobacter baumannii, Staphylococcus aureus* and enterococci.

Community-acquired sepsis is also an important cause of fever among patients admitted to hospitals across South and Southeast Asia. In our practice, community-acquired sepsis is defined as the presence of sepsis with a confirmatory blood culture collected within 48 hours after hospital admission.^14^ Distinguishing bacterial infections from other common causes of fever, such as malaria or dengue, can be challenging without diagnostic laboratory support.^15^ Important causes of community-acquired bloodstream infection (CA-BSI) in LMICs include *Salmonella* serovars Typhi and Paratyphi A, *E. coli*, *K. pneumoniae*, *S. aureus* and *Streptococcus pneumoniae*. We have reported increasing levels of AMR in these common community-acquired pathogens and highlighted the difficulties of accurate diagnosis with traditionally available diagnostics. For example in Nepal and Vietnam antimicrobial resistance in *Salmonella* Typhi and *Salmonella* Paratyphi A has severely restricted the options available for antimicrobial treatment.^16^

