### Primary objectives

To describe the clinical characteristics of neonates with sepsis, including community and hospital-acquired sepsis, early-onset and late-onset sepsis.To determine the aetiology of neonatal sepsis and the distribution of pathogens by clinical departments including the Neonatology Department and the Neonatal Intensive Care Unit.To determine the antimicrobial susceptibility profiles of the bacteria causing neonatal sepsis and the AMR profiles occurring in community and hospital-acquired infections.To analyse the impact of specific bacteria and AMR profile on the outcomes (mortality, length of stay and cost of treatment) of neonates with sepsis.To determine the genome sequences of bacterial strains associated with neonatal sepsis.

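### Excluding stays under 24 hours and imminent deaths selects on outcomes of a primary objective: cohort mortality is probably understated, and comparisons by place of acquisition or resistance may be distorted by an unknown amount

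*Protocol article*

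**What the plan says.** The Exclusion criteria section removes infants without consent, infants already recruited, and those meeting either of two further rules: "the length of hospital stay less than 24 hours, imminent and inevitable death". It then adds a safeguard: "Investigators will review all of the mortality records during the time period of the study". The stated purpose is to find how many such cases were missed and whether they had features in common.

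The fourth item under Primary objectives is "To analyse the impact of specific bacteria and AMR profile on the outcomes (mortality, length of stay and cost of treatment) of neonates with sepsis". Table 2 (Study summary) also lists mortality, length of stay and cost, and refers them to hospitalised neonates generally. The third primary objective covers "the AMR profiles occurring in community and hospital-acquired infections".

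Place of acquisition is defined in the section Sepsis and AMR in Vietnam. Hospital-acquired sepsis requires "a confirmatory blood culture collected >48 hours following hospital admission"; community-acquired sepsis requires "a confirmatory blood culture collected within 48 hours after hospital admission".

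**The concern.** Both rules select on what the study sets out to measure. A stay under 24 hours is known only once the infant has died or left, and it includes every death on the first day. The second rule selects on expected death. An infant who dies of sepsis within 24 hours of admission does not count towards mortality, length of stay or aetiology.

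The 24-hour rule also acts on one side only. A community-acquired infant cultured at admission must remain in hospital alive for 24 hours to be counted. A hospital-acquired infant has already been in hospital for more than 48 hours when cultured, and passes the rule even if death follows within hours. The article's section on Southeast Asia links multidrug resistance particularly to healthcare-acquired infection, so an imbalance by acquisition could carry over into a crude comparison of resistant with susceptible infections.

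At stake are the reported mortality, the place of rapidly fatal organisms in the aetiology, and the reading of resistance against death.

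**Working it through.** **Inputs.** From the article: 800 expected participants and about 400 isolates (Sample size), plus the definitions above. The 800 is a recruitment forecast from surveillance data, not a power calculation, so there is no figure to reproduce. The article gives no mortality rate, early-death fraction or number of excluded infants. Every value of m, x, d, e, f, g and resistance prevalence below is an assumption.

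**Step 1: who the 24-hour rule can remove.** Hospital-acquired means cultured after 48 hours, so the stay exceeds 48 hours and cannot be under 24. On a single admission clock, the rule removes no culture-confirmed hospital-acquired case. Three limits apply:
- The imminent-death rule and the consent requirement can remove either class.
- Probable sepsis needs no positive culture and gets no class from these definitions. With 400/800 = 50% expected yield, that may be about half the cohort.
- Time spent in a referring hospital is not addressed.

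**Step 2: overall mortality.** With enrolled mortality m, and x excluded infants of whom a share d died, mortality in all eligible infants is (800m + xd)/(800 + x).

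| Enrolled m | x = 8, d = 50% | x = 80, d = 100% |
|---|---|---|
| 5% | 44/808 = 5.4% | 120/880 = 13.6% |
| 10% | 84/808 = 10.4% | 160/880 = 18.2% |
| 20% | 164/808 = 20.3% | 240/880 = 27.3% |

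At m = 15%, adding e missed deaths gives (120 + e)/(800 + e): 136/816 = 16.7%, 162/842 = 19.2% and 200/880 = 22.7% for e = 16, 42 and 80. If the excluded die at the enrolled rate there is no bias. If none of them died, the enrolled figure is too high (m = 10%, x = 80: 80/880 = 9.1%). So mortality is understated if and only if the excluded die more often than the enrolled. That is essentially certain under the imminent-death rule and plausible, but undocumented, under the 24-hour rule.

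**Step 3: mortality by acquisition.** Let true mortality m be equal in both classes. Losing a fraction f of community-acquired deaths leaves observed mortality m(1−f)/(1−mf) and odds m(1−f)/(1−m). Losing a fraction g of hospital-acquired deaths leaves odds m(1−g)/(1−m). The spurious hospital-to-community odds ratio is (1−g)/(1−f), whatever m is.

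| f | g | Spurious odds ratio |
|---|---|---|
| 10% | 0 | 1.11 |
| 20% | 0 | 1.25 |
| 40% | 0 | 1.67 |
| 40% | 20% | 0.80/0.60 = 1.33 |
| 40% | 40% | 1.00 |
| 20% | 40% | 0.60/0.80 = 0.75 |

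At m = 15%, f = 40% and g = 0, community mortality appears as 0.09/0.94 = 9.6% against 15%.

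**Step 4: resistance and mortality.** Assume resistance in 30% of community and 70% of hospital cases, classes of equal size, no true effect of either factor, and g = 0. The crude odds ratio is (1 − 0.3f)/(1 − 0.7f): 1.04, 1.12 and 1.31 for f = 10%, 25% and 50%. Within each acquisition class it stays 1.

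Now let early loss depend on resistance itself, with a true odds ratio of 2.0. Equal loss leaves 2.0. Losing 30% of deaths in resistant and 10% in susceptible cases gives 2.0 × 0.70/0.90 = 1.56. The reverse gives 2.0 × 0.90/0.70 = 2.57.

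**The case against.** The authors saw the problem: the record review stands beside the exclusions, and the article's limitations mention the ethics of sampling severely ill neonates. The article is condensed, and a sensitivity table could sit in an analysis plan that is not shown. This stands in part. The absence of such a table is not itself the finding. But the role that the article gives the review is to count and describe, which leaves the estimates as they were, and mortality records cannot show infants who left alive within 24 hours.

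A reader might infer that hospital-acquired infection is bound to look more lethal. The documents do not support that. It would need early deaths to be lost only from the community group, whereas the imminent-death and consent rules can also remove hospital-acquired deaths. Nor is a mortality comparison by acquisition a named analysis: acquisition class appears in the objectives on clinical characteristics and resistance profiles, and Statistical comparisons lists culture result, Gram stain and survival before ending with an open list.

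A reader might also infer that the resistance–mortality results are biased upwards. That too is conditional. It needs either an analysis not stratified by acquisition or early loss that differs by resistance, and in the latter case the bias can go either way.

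Finally, removing the 24-hour exclusion looks like the natural remedy. Recruitment has run since January 2017, so a change would mix two eligibility rules, and consent would still be needed, so many first-day deaths might not be recovered.

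**Conclusion.** The point holds in a limited form. The two exclusions select on outcomes of a primary objective. Enrolled-cohort mortality is probably understated for all neonates admitted with sepsis, and rapidly fatal pathogens may be under-represented. The 24-hour rule, unlike the imminent-death rule, cannot touch a culture-confirmed hospital-acquired case, provided one admission clock is used. A mortality comparison by acquisition, or a resistance–mortality comparison that ignores acquisition, may therefore be distorted.

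The size is not known. Under the assumed inputs, adding back excluded infants moves a 10% mortality to between 10.4% and 18.2%, and the spurious acquisition odds ratio runs from 0.75 to 1.67. These figures show sensitivity and are not estimates. For an observational study with largely descriptive aims, this is a cheap improvement rather than a fault that must be repaired before the study can be used.

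**What to change.** Keep the eligibility rules and make four changes in the analysis wording:

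1. Use the planned mortality-record review to tabulate missed septic deaths as de-identified counts by organism, resistance and, where a culture exists, acquisition class.
2. Report mortality, and the pathogen and resistance contrasts with outcome, with and without these deaths. Say that the version with them adds deaths but not infants who left alive within 24 hours, so in that respect it leans high.
3. Stratify or adjust the resistance–mortality analyses by acquisition class.
4. State the target population of the main estimates as consented neonates staying at least 24 hours.

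A 24-hour landmark after the index culture is at most a sensitivity analysis. As the main comparison it would discard further deaths in both groups and deepen the conditioning on survival.

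The cost is one supplementary table with few covariates, some linkage of records to culture results, and possibly confirmation from the ethics committees that de-identified counts may be used. The review itself is already planned.

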### Identification of participants

All doctors and nurses in the Department of Neonatology and Neonatal Intensive Care Unit of the study hospital will be informed about, and trained for, this clinical investigation. In addition, those working in the Department of Neonatology and Neonatal Intensive Care Unit will also be involved in the study. These staff will be trained to identify eligible patients and how to notify investigators.

### Informed consent

Trained, Good Clinical Practice (GCP) accredited, members of the study team will collect informed consent. The team will discuss the study with the accompanying parent/guardian, or, if both parents are deceased or not actively involved in child care, the main long-term carer of the child will be accepted as the guardian and considered able to give consent for the study. Study staff will describe the purpose of the study, the study procedures, possible risks/benefits, the rights and responsibilities of participants and alternatives to enrolment. The parent/guardian will be invited to ask questions, which will be addressed by study staff, and they will be provided with appropriate contact numbers if they have any subsequent questions. If the parent/guardian agrees for the child to participate, they will be asked to sign and date an informed consent form. A copy of the patient information sheet and the informed consent form will be given to them to keep. In addition to the procedures above, illiterate signatories will have the informed consent form read to them in the presence of a witness who will sign to confirm this. The parent/guardian can withdraw from the study at any time (verbally) without affecting the care that the child will receive. If the parent/guardian decides at any time to take the child out of the study, no new information will be collected. However, information collected on the child up until that point will still be used. All patient information sheets and consent forms will be written in the local language and will use terms that are easily understandable.

### Study procedures

An investigator will routinely record and collect demographic, clinical and laboratory information of the patients, the date of blood draw, the number of blood culture bottles inoculated, the result of the culture (whether positive or negative) and the susceptibility of the isolate to commonly used antimicrobials. Data from these records will be subsequently entered into CliRes Data Management System of OUCRU. These will be source data for this study. The number of patients admitted to the hospital annually will be obtained from hospital records. As part of this study, we request that all isolates from blood are stored and archived at –80°C. These isolates will be recultured and the identification will be reconfirmed. Selected isolated organisms from blood will have further molecular characterisation at a later date.

## Data collection

### Demographic and clinical assessments

Data on neonatal sepsis at Children’s Hospital 1 will be collected to the case report form. These data will include administrative data, demographic data, clinical characteristics, laboratory results, diagnoses, treatments and outcomes. The Neonatal Therapeutic Intervention Scoring System will be used to estimate the disease severity.^23^

### Microbiological assessments

Available routine microbiology data on neonatal bloodstream infections Children’s Hospital 1. These data will include pathogenic agents isolated from blood culture and antimicrobial susceptibility profile of isolated bacteria (routine panel of antimicrobials). Selected isolates will have additional antimicrobial susceptibility testing, molecular analysis for antimicrobial resistance genes and genome sequencing of selected strains defined by antimicrobial susceptibility data.

## Laboratory methods

### Microbiology testing

When required for checking or to non-routine antimicrobials, antimicrobial susceptibility testing of the pathogens isolated will be performed by disk diffusion using guidelines established by the Clinical and Laboratory Standards Institute and, when required, by minimum inhibitory concentration estimation using the VITEK 2 COMPACT automated machine. Antimicrobial susceptibilities tested will include nalidixic acid, ciprofloxacin, ceftriaxone, cefepime, ampicillin, trimethoprim–sulfamethoxazole, azithromycin, imipenem, colistin and amikacin for all Gram-negative organisms and oxacillin and vancomycin in Gram-positive organisms. The production of extended-spectrum beta lactamases (ESBL) will be investigated using the double-disc synergy test by comparing zone sizes between ceftazidime discs against ceftazidime–clavulanic acid discs and cefotaxime discs against cefotaxime–clavulanic acid discs. Isolates with an increase in diameter of inhibitory zone of equal to or more than 5 mm by the synergy of clavulanate will be considered ESBL positive.

Organisms including coryneforms (*Corynebacterium*, etc), *Micrococci*, *Propionibacterium*, *Bacillus*, alpha haemolytic *Streptococci*, environmental Gram-negative bacilli and non-pathogenic *Neisseria* will be considered potential contaminants. The pathogen-contaminant decision will be made based on the clinical relevance of the isolated bacteria and the independent assessments by two qualified medical microbiologists. If there is disagreement, then the case will be discussed until a decision is reached.

### Bacterial storage

Organisms will be subcultured onto 5% blood agar and the purity of the isolate will be tested before storage in 20% glycerol at –80°C.

### Isolation of nucleic acids

Isolates will be recultured and their identification rechecked. DNA will be extracted from bacterial isolates using the Wizard Genomic DNA Extraction Kit (Promega, Fitchburg, Wisconsin, USA). The quality and concentration of the DNA will be assessed using a nanodrop spectrophotometer prior to PCR amplification and the Quant-IT Kit (Invitrogen, Carlsbad, California, USA) prior to DNA sequencing.

### PCR for resistance genes

The primary focus study is to investigate the distribution of antimicrobial resistance genes in bacteria causing neonatal sepsis. Therefore, all Gram-negative organisms will be investigated by PCR to detect genes catalysing resistance to cephalosporins, fluoroquinolones and carbapenems. Conventional PCR will be performed for the following classes of resistance genes using previously described methods. The multiplex and monoplex PCRs are described in these publications. PCR will be used to detect AmpC, ESBL (including CTX-M15), NDM, qnr, OXA, KPC and mecA/Van.^11 24–29^

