### Secondary objectives

To determine the AMR profiles and gene distribution of isolated bacteria by clinical departments to add insight into the circulation of bacteria associated with hospital acquired infections.To study the genes catalysing resistance to antimicrobials commonly used to treat neonatal sepsis (specifically third/fourth generation cephalosporins, fluoroquinolones and carbapenems).

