### Antimicrobial resistance genes and genome sequencing

The presence/absence of antimicrobial resistance genes will be reported as proportions per organism and then stratified by organism, year and hospital department. Genome sequences will be determined to study phylogenetic relationships, the presence/absence of virulence genes and also AMR gene content and first analysed by species and then group by their Gram-stain results. Briefly, for phylogenetic analysis, chromosomal single nucleotide polymorphism (SNP) alleles will be concatenated for each strain to generate a multiple alignment of all SNPs. For maximum likelihood (ML) analysis, RAxML will be run using the generalised time-reversible model and 1000 bootstrap pseudoreplicate analyses were performed to assess support for the ML phylogeny. Root-to-tip branches will be extracted from the ML tree using the programme TreeStat. The relationship between root-to-tip distances and year of isolation will be analysed using linear regression. For Bayesian Evolutionary Analysis Sampling Trees (BEAST) analysis (V1.6), a GTR+Γ substitution model and defined tip dates as the date of isolation will be used.^30 31^ To detect the presence or absence of genes read sets will be assembled using the de novo short read assembler Velvet and Velvet Optimizer. Organism specific read sets will then be aligned to the pangenome. Taxonomic investigation of accessory and AMR genes will be performed using MG-RAST V.3.2.

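### The stated genotypic methods for fluoroquinolone resistance, *qnr* PCR and gene presence/absence, cannot register target-site mutations

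*Protocol article*

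**What the plan says.** Secondary objectives (Protocol article) include this aim: "To study the genes catalysing resistance to antimicrobials commonly used to treat neonatal sepsis (specifically third/fourth generation cephalosporins, fluoroquinolones and carbapenems".

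The section on PCR for resistance genes takes up the same three classes: "all Gram-negative organisms will be investigated by PCR to detect genes catalysing resistance to cephalosporins, fluoroquinolones and carbapenems". It then lists the targets: "PCR will be used to detect AmpC, ESBL (including CTX-M15), NDM, qnr, OXA, KPC and mecA/Van".

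The section on antimicrobial resistance genes and genome sequencing sets the readout: "The presence/absence of antimicrobial resistance genes will be reported as proportions per organism and then stratified by organism, year and hospital department". It gives the purposes of sequencing: "Genome sequences will be determined to study phylogenetic relationships, the presence/absence of virulence genes and also AMR gene content". SNPs appear once, with one stated use: "for phylogenetic analysis, chromosomal single nucleotide polymorphism (SNP) alleles will be concatenated for each strain to generate a multiple alignment of all SNPs". In the same section, the presence or absence of genes is to be established from de novo assemblies and alignment to a pangenome.

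Three other places matter. Microbiology testing puts nalidixic acid and ciprofloxacin in the susceptibility panel for Gram-negative organisms. The Abstract (Method and analysis) announces that clinical variables and outcomes will be compared by AMR gene content. On the extent of sequencing the article disagrees with itself: the Abstract has every blood isolate sequenced, whereas Microbiological assessments and Genome sequencing speak of selected isolates.

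**The concern.** Acquired resistance genes are either in an isolate or not, so a presence/absence readout suits them. Fluoroquinolone resistance can also arise by point mutation in chromosomal target genes, which susceptible isolates carry too. Presence or absence of such a gene says nothing about whether it is mutated. Where this mechanism operates, the stated method does not measure what the objective names for that class.

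Two outputs would be affected. Fluoroquinolone determinants tabulated by organism, year and department would be understated, possibly unevenly across strata if the mix of mechanisms differs between them. In comparisons by AMR gene content, isolates resistant only by mutation would be pooled with those that have no fluoroquinolone determinant, which blurs the contrast. The genotype tables could also disagree with the ciprofloxacin and nalidixic acid results for no reason that the reader could see.

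**Working it through.** The article states no figure on this point: no fluoroquinolone resistance rate, no *qnr* frequency and no share of resistance due to mutation. There is nothing to reproduce, so the check is a reading of the passages followed by a range.

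**Step 1. Can any stated genotypic step show a target-site mutation?**

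- PCR panel: *qnr* is the only fluoroquinolone target, and no target-site locus is listed.
- Reporting rule: presence or absence of resistance genes.
- Genome analysis: AMR gene content from assemblies, which again records presence or absence.
- SNPs: derived, but the stated use is the phylogenetic alignment.

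None of these steps calls resistance mutations. The reads from sequenced isolates would nevertheless cover the chromosomal target genes, so the information would exist without a stated step to extract it.

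**Step 2. What share of resistant isolates could be left without a determinant?**

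Let *q* be the share of fluoroquinolone-resistant Gram-negative isolates that carry a listed acquired gene (*qnr*). Let *w* be the share of the remainder that is sequenced and has its mutations called and found. Then

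unexplained share = (1 − *q*) × (1 − *w*).

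Both *q* and *w* are assumptions. The stated methods correspond to *w* = 0.

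| *q* (assumed) | *w* = 0 | *w* = 0.5 | *w* = 1 |
|---|---|---|---|
| 0.1 | 90% | 45% | 0% |
| 0.3 | 70% | 35% | 0% |
| 0.5 | 50% | 25% | 0% |
| 0.7 | 30% | 15% | 0% |
| 0.9 | 10% | 5% | 0% |

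With *w* = 0 the unexplained share is a majority only if *q* is below 0.5.

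**Step 3. Counts.**

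The Sample size section expects about 400 isolates. The Gram-negative share *g* and the resistant share *r* are again assumptions. The number unexplained at *w* = 0 is 400 × *g* × *r* × (1 − *q*).

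- Middle case, *g* = 0.5 and *r* = 0.5: 400 × 0.5 × 0.5 = 100 resistant isolates, of which 90, 50 or 10 are unexplained at *q* = 0.1, 0.5 or 0.9.
- Lowest corner, *g* = 0.3, *r* = 0.2, *q* = 0.9: 400 × 0.3 × 0.2 × 0.1 = 2.4, about 2.
- Highest corner, *g* = 0.7, *r* = 0.5, *q* = 0.1: 400 × 0.7 × 0.5 × 0.9 = 126.

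The count could be trivial or large, and the documents do not say which.

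**The case against.** The strongest reply has four parts.

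*Fluoroquinolone resistance is not studied by genotype alone.* This stands. Ciprofloxacin and nalidixic acid susceptibility are tested, and the AMR profiles in the primary objectives can rest on those results. A reader might infer that the study measures fluoroquinolone resistance only through *qnr*. The documents do not support that, and the point is confined to the genotypic objective.

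*The plan never defines a fluoroquinolone-resistance genotype.* This also stands. No passage classifies an isolate as resistant or susceptible from its *qnr* result, and the proportion carrying *qnr* is a correct statement about *qnr*. It would be wrong to say that the plan misclassifies phenotype. The gap is between that proportion and an objective that names the whole class. The objective's wording could be read as covering acquired genes only; if that is intended, the article should say so and label the result accordingly.

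*The size is assumed.* This stands as well. A reader might infer that most resistant isolates would be left without a determinant. That needs *q* below 0.5 and no mutation calling, and the documents give no value for *q*. That target-site mutation is a mechanism at all is general microbiology, which the article does not discuss.

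*A journal article condenses its methods, and mutation calling may be in a fuller document.* This stands in part. The pipeline is given in brief, and nothing excludes a second use of the SNPs. But the article does not leave the matter open: it names the PCR targets, the readout, the assembly step and the use of the SNPs. What it does specify cannot register this mechanism.

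**Conclusion.** For the genotypic study of fluoroquinolone resistance, the stated methods cannot register point mutations in chromosomal target genes. Isolates resistant only by that route would fall in the determinant-negative group in the stratified gene tables and in comparisons by AMR gene content. This follows from the stated methods and needs no outside figure beyond the fact that the mechanism exists.

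The size is unknown. The 10% to 90% range is simply the complement of assumed *qnr* shares of 90% to 10% with no mutations called; it is not an estimate. It shrinks as more isolates are sequenced and called. The point does not touch the sample size, the phenotypic AMR profiles or any error rate. It is worth correcting because fluoroquinolones are one of three classes named in the objective, the gene results feed comparisons of outcome, and the correction is cheap.

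**What to change.** In the analysis section on antimicrobial resistance genes and genome sequencing:

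1. Add calling of target-site mutations (*gyrA*, *parC* and species equivalents) from the reads that the study already plans to generate.
2. In sequenced isolates, report these mutations together with acquired fluoroquinolone-resistance genes, set against the ciprofloxacin and nalidixic acid phenotype, with the number of isolates in the denominator stated.
3. Where an isolate has PCR only, report the result as *qnr* carriage, not as fluoroquinolone-resistance genotype.
4. Reconcile the Abstract (all isolates sequenced) with Microbiological assessments and Genome sequencing (selected isolates), since this determines the denominator in item 2.

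The cost is some additional bioinformatics on planned data and a change of wording; no new assay is needed. The downside is that the combined genotype exists only for sequenced isolates. If these remain a selected subset, the denominator is smaller. Because Genome sequencing selects partly on susceptibility profile and resistance gene content, proportions from that subset should then not be presented as proportions of all isolates.
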